#### Analysis

At the first time point (T1), we will compare addiction stigma, optimism, hope, and warmth toward subject scores between the 2 intervention groups and the control group. This comparison is intended to establish the immediate effect of watching the intervention videos on addiction stigma, optimism, hope, and warmth toward people with addiction. At the second time point (T2), we will once again compare our primary and secondary outcomes between the intervention and control groups. This will allow us to detect potential short-term effects of watching the intervention video on addiction stigma, optimism, hope, and warmth toward people with addiction. By comparing the outcomes of the 2 intervention arms at the 2 time points, we will be able to measure the contribution of sound design to the effect of the SAS video intervention.

#### Sample Size

We calculated the sample size needed for comparing mean scores between the 3 arms, as detailed in the trial design. This was performed independently for the primary and secondary outcomes based on the score of each survey, upon which we selected the most conservative sample size for our study.

We assume that a significant, sustainable change in addiction stigma from watching the SAS video could be achieved by multiple exposures to the video or similar SAS interventions in a series of “micro-doses.” As our study measures the effect of a single exposure to a single SAS video, we aim to measure a small change in our mean outcome scores, presuming that these small changes could yield larger ones following repeated exposures (microdoses). Thus, we have powered this trial to detect a small effect size for comparing the mean scores between trial arms, that is, *d*=0.1, smaller than the generally recommended threshold for detecting a small effect size [31].

We used the sample size formula for a 1-tailed comparison of the mean scores with equal variance, a Type I error of 0.01 to account for multiple comparisons, and a power of 80% to detect changes in the mean scores. This resulted in a sample size of 1128 individuals per arm. Accounting for a potential attrition rate of 20% (personal communication with ProA), this yields 1410 individuals per arm. For this study, we will recruit 1500 participants per arm in each of the 3 countries. This gives us a total sample size of 13,500 participants, which allows us to detect the potential effects of the intervention with a power higher than 80%.

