### Intervention

This short, animated story video was co-created by a global health communication specialist with formal training in screenwriting and story development, an addiction medicine specialist, a professional animator living in South Africa, an adolescent composer and sound designer, and a group of high school student advisors at Avenues the World School in New York City. The intervention follows a classical 3-act story structure, with an inciting event, rising action, a midpoint, climax, and resolution. Figure 2 displays selected scenes from the SAS intervention video, with corresponding timestamps and descriptions of the story “beats” that propel the narrative forward. The main character is a fish who discovers and tries a foreign substance, ignoring the warnings of a more senior fish character. The young fish soon becomes addicted to the substance, and we see the negative impact on his underwater life. He injures others around him while under the influence and, finally, injures himself in his desperate pursuit of the next high. In this way, the video visually conveys the concept of drug tolerance. In the second half of Act 2, the main character, in desperation, gulps down the remaining dose of the addictive substance before realizing that he is (literally) hooked. A fishing line drags him off-screen and it seems that all is lost until the senior fish reappears and helps him break free of the hook. This leaves a deep gash in the young fish’s mouth. In the young fish’s moment of deepest pain and shame, the senior fish reveals his identical gash (the unexpected story twist). The 2 fish share a moment of painful empathy, then swim off-screen together. The only words in this video appear as text on the final, “call-to-action” screen: “Hooked on something that’s hurting you? Speak up. There’s help.” The video can be viewed on YouTube [24].

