#### Sequence Generation, Allocation Concealment, and Implementation

This 3-arm individual, parallel-group randomized controlled online trial will be hosted and implemented by the Qualtrics survey platform. The platform uses a computer-generated allocation sequence to randomly allocate participants 1:1:1 to the 3 trial arms. The investigators will remain unaware of individual trial arm allocations.

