##### Primary Outcomes

For each participant, stigma scores will be calculated individually. The mean score for each study arm at T1 and T2 will be calculated and compared between the intervention arms and the control arm at T1, and between the intervention arms and the control arm at T2, using repeated measure ANOVAs. This will be done at the study level and the country level to identify differential effectiveness across geographic conditions. We will also use multilevel regression analyses to control for demographic factors and other potential variables as needed. All analyses will be conducted in R (R Core Team, 2021).

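### Sample size and power are stated for a 1-tailed test at 0.01, but the primary analysis is a non-directional repeated-measures ANOVA, so the stated power belongs to a more favourable test than the one planned

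*Protocol article*

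**What the plan says.** The Sample Size section bases the calculation on a directional test: "We used the sample size formula for a 1-tailed comparison of the mean scores with equal variance, a Type I error of 0.01". The level is meant to allow for multiple comparisons, and it is paired with "a power of 80% to detect changes in the mean scores", for a standardised difference of d=0.1, described as "smaller than the generally recommended threshold for detecting a small effect size". The result is 1128 per arm, or 1410 after 20% attrition. The plan recruits 1500 per arm in each of three countries (13,500 in total) and concludes that power exceeds 80%. It does not say whether that holds for the pooled analysis, for each country, or for both.

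The Primary Outcomes part of the statistical methods compares mean stigma scores of the intervention arms with control at T1, and "between the intervention arms and the control arm at T2, using repeated measure ANOVAs". This is done for the whole study and by country, with multilevel regression as a further analysis. That section gives neither a direction nor an error level. The article's only mention of a 1-tailed test is as an input to the sample size formula.

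**The concern.** An ANOVA F test responds to differences in either direction, as does a pairwise contrast from the model at its usual two-sided level. A 1-tailed test at 0.01 puts all its error on one side. Its critical value of 2.33 is that of a two-sided test at 0.02, while a two-sided test at 0.01 needs 2.58. A benefit with z between 2.33 and 2.58 is therefore significant under the sizing assumption but not under a two-sided test at the same nominal level.

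What is at stake is the power claim. A reader will take it to describe the planned primary analysis, including the country-level analyses, but it was derived for a test that the analysis section does not name and that is easier to pass in the hoped-for direction.

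**Working it through.** **Inputs from the protocol article.** d=0.1, alpha 0.01, 1-tailed, power 80%, attrition 20%, 1500 recruited per arm per country (Sample Size). Allocation: "randomly allocate participants 1:1:1 to the 3 trial arms" (Sequence Generation, Allocation Concealment, and Implementation). Retained at T2: 1500 × 0.8 = 1200 per arm in one country, and 3 × 1200 = 3600 per arm pooled.

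**The plan's own figure.** With SD=1, n per arm = 2(z_alpha + z_power)²/d².
- One-sided 0.01: 2 × (2.326 + 0.842)²/0.01 gives 2008, not 1128.
- Two-sided 0.01: 2 × (2.576 + 0.842)²/0.01 gives 2336.
- The attrition step does reproduce: 1128/0.8 = 1410.

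So 1128 does not follow from the stated inputs under either sidedness. At 1128 per arm, power for d=0.1 is 51.9% one-sided and 42.0% two-sided.

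**Power at the actual sample size.** Power = Φ(d·√(n/2) − z_crit), with z_crit = 2.326 one-sided or 2.576 two-sided.

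| Analysis | n per arm | d·√(n/2) | One-sided 0.01 | Two-sided 0.01 | Difference |
|---|---|---|---|---|---|
| One country, T2 | 1200 | 2.449 | 54.9% | 45.0% | 9.9 points |
| One country, T1, no attrition | 1500 | 2.739 | 66.0% | 56.5% | 9.5 points |
| Pooled, T2 | 3600 | 4.243 | 97.2% | 95.2% | 2.0 points |
| Pooled, T1, no attrition | 4500 | 4.743 | 99.2% | 98.5% | 0.7 points |

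**Splitting the country-level gap at T2.** From 80% to 45.0% is 35 points. About 25 (80 − 54.9) remain even with the 1-tailed test and come from the sample size figure. About 10 (54.9 − 45.0) come from sidedness.

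**Omnibus F or pairwise contrast.** For a one-way, three-arm F test at 0.01 at a single time point, with 0.1 between the highest and lowest arm, power is 34.5% to 48.6% in one country (1200 per arm) and 91.1% to 97.7% pooled (3600 per arm). The value depends on whether the third arm lies midway or at one end. Which result is read as the primary one therefore matters as well.

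**Sensitivity to the model.** A baseline-adjusted analysis multiplies the variance by 1 − ρ², where ρ is the within-person correlation. The article gives no ρ, so these values are assumptions. At 1200 per arm, two-sided 0.01:
- ρ=0: Φ(2.449 − 2.576) = 45%.
- ρ=0.5: Φ(2.449/√0.75 − 2.576) = Φ(0.25) = 60%.
- ρ=0.7: Φ(2.449/√0.51 − 2.576) = Φ(0.85) = 80%.

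Bringing 2008 down to 1128 would take ρ = √(1 − 1128/2008) = 0.66.

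**The case against.** The hypotheses are directional (the video should lower stigma), so sizing on one tail has a rationale. Sizing on a simple comparison of two means and analysing with a fuller model is ordinary practice. The direction and level of the final tests are often left to a statistical analysis plan, which may exist and is not shown. All of this stands, so the silence of the analysis section is not in itself a fault. What it does not remove is the mismatch in the article: a power statement is made for one kind of test and a different kind is named for the analysis.

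A reader might go further and infer that the decision rule is undefined, or that a video that raises stigma could not be declared harmful. The worry is easy to form, since the story includes the line "He injures others around him while under the influence and, finally, injures himself in his desperate pursuit of the next high" and the AQ-18 scores blame, dangerousness, fear and avoidance. The documents do not support either inference. The planned ANOVA rejects for a rise in stigma as readily as for a fall, and the arm means show which occurred. Only a 1-tailed analysis would be blind to a rise (rejection probability below 0.000001 for a rise of d=0.1 with 1200 per arm), and no section plans one. The same story also ends in rescue and shared empathy, and the article gives no data that point to an increase in stigma.

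**Conclusion.** The concern holds as an inconsistency between sizing and analysis. The power statement belongs to a more favourable test than the non-directional one planned. Sidedness alone costs about 2 points pooled and about 10 points within a country at T2.

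The pooled analysis keeps well over 80% power either way. The country-level analysis does not reach 80% under either sidedness in a simple comparison, and that shortfall is mostly due to the separate error in the 1128 figure.

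These figures assume d=0.1, alpha 0.01, the full 20% attrition at T2, equal variances and no gain from repeated measures or baseline adjustment. A model that uses the within-person correlation could have higher power, by an amount that the article gives no basis for fixing.

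**What to change.** In the Sample Size section and in the Primary Outcomes part of the statistical methods, state that arm contrasts are two-sided at 0.01, that they are read from the pairwise contrasts of the model, and that significant differences in either direction are reported as such.

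In the Sample Size section, restate power for that test at the actual sample size. For a simple comparison of two means with d=0.1 and 20% attrition, this is about 95% pooled (3600 per arm) and about 45% within one country (1200 per arm), in place of one undifferentiated claim of more than 80%. If a baseline-adjusted or repeated-measures model is relied on for more power, give the assumed correlation and its source. Correct the 1128 at the same time, since the restated figures cannot be reconciled with it.

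The cost is wording only, with no extra participants, if the 80% claim is limited to the pooled analysis. Keeping that claim for each country under an unadjusted two-sided test would need 2336 per arm, or 2336/0.8 = 2920 after attrition, against the 1500 planned.

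### The stated 1128 per arm does not follow from the printed inputs, which give about 2008; power above 80% for d=0.1 holds pooled over countries but not for an unadjusted comparison within one country

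*Protocol article*

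**What the plan says.** The Sample Size section prints every input that the two-sample formula needs.

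- Effect size: "that is, *d*=0.1, smaller than the generally recommended threshold for detecting a small effect size".
- Test: "We used the sample size formula for a 1-tailed comparison of the mean scores with equal variance".
- Error rates: "a Type I error of 0.01 to account for multiple comparisons, and a power of 80% to detect changes in the mean scores".
- Result: "This resulted in a sample size of 1128 individuals per arm".

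A 20% attrition allowance raises this to 1410 per arm. The section then sets recruitment at 1500 per arm in each of three countries, 13,500 in all, "which allows us to detect the potential effects of the intervention with a power higher than 80" per cent.

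The section also says that the calculation was done separately for each outcome and that the most conservative result was kept. It mentions no baseline correlation, paired design or other reduction of variance.

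Under Statistical Methods, Primary Outcomes, the arms are to be compared at T1 and at T2 "using repeated measure ANOVAs", both for the whole study and within each country.

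**The concern.** The result looks too small for its inputs. A standardised difference of 0.1 at one-tailed 0.01 is demanding, and 1128 is below even what one-tailed 0.05 would require.

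This figure is the printed justification for the size of the trial. Because 1410 is rounded up to 1500 in each country, the per-arm requirement appears to have been applied country by country, and the country-level comparison is a planned analysis. If 1128 is too low, a reader would credit the country-level comparisons with power that the printed assumptions do not give them. The pooled comparison, with three times as many participants per arm, is a separate matter and has to be checked on its own.

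**Working it through.** **Inputs.** From Sample Size: d = 0.1 (SD = 1 on the standardised scale), one-tailed alpha 0.01, power 80%, attrition 20%, 1500 recruited per arm per country. From Sequence Generation: 1:1:1 allocation. From the recruitment and retention section: pilot retention 88% (526/598).

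**The plan's own figure.** For two equal arms, n per arm = 2 × (z for alpha + z for power)² / d².

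- One-tailed 0.01: 2 × (2.326 + 0.842)² / 0.01 = 2007.2, so 2008. The plan states 1128, about 44% lower (1 − 1128/2008).
- Attrition: 1128/0.8 = 1410, which reproduces the plan. The same step applied to 2008 gives 2510.

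**Other settings at d = 0.1 and 80% power.**

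| Setting | n per arm |
|---|---|
| two-tailed 0.01 | 2336 (2920 after attrition) |
| two-tailed 0.05 | 1570 |
| one-tailed 0.05 | 1237 |
| one-tailed 0.10 | 902 |
| one-sample or paired, one-tailed 0.01 | 1004 |
| one-sample or paired, two-tailed 0.01 | 1168 |

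None gives 1128.

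**What would give 1128, changing one input at a time.**

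- Effect size: d = √(2/1128) × 3.168 = 0.133.
- Alpha: 0.1 × √(1128/2) − 0.842 = 1.533, a one-tailed alpha of about 0.063.
- Baseline adjustment, which multiplies n by 1 − r²: r = √(1 − 1128/2007.2) = 0.66.

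**Power at d = 0.1, unadjusted.** Power = Φ(d × √(n/2) − z for alpha), with z = 2.326 one-tailed and 2.576 two-tailed at 0.01. For n = 1200, one-tailed: 0.1 × √600 − 2.326 = 0.123, and Φ(0.123) = 0.549.

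| Comparison | n per arm | One-tailed | Two-tailed |
|---|---|---|---|
| n as stated | 1128 | 52% | 42% |
| Country, T1, no loss | 1500 | 66% | 56% |
| Country, T2, 88% retained | 1320 | 60% | 50% |
| Country, T2, 20% attrition | 1200 | 55% | 45% |
| Pooled, T2, 20% attrition | 3600 | 97% | 95% |

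**Detectable d at 80% power with 1200 per arm.** One-tailed: √(2/1200) × 3.168 = 0.129. Two-tailed: √(2/1200) × (2.576 + 0.842) = 0.140.

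**Effect of baseline adjustment (r is an assumption; the documents give none).** One-tailed power within a country reaches 80% when n = 2007.2 × (1 − r²). That means r = √(1 − 1500/2007.2) = 0.50 at T1 with no loss, 0.59 with 1320 per arm and 0.63 with 1200 per arm. At r = 0.3 and r = 0.5, 1200 per arm gives about 60% and 69%.

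**The case against.** Four points can be made for the protocol.

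- **The power claim is tied to the total.** No sentence promises more than 80% within a country, and for the pooled comparison the claim is correct with room to spare. This stands. A reader might infer that the power statement is false, but the documents do not support that. What is wrong is the per-arm figure; the country-level shortfall follows from the sizing of 1500 per arm in each country and from the planned country-level analysis.
- **55% is not the country-level power in general.** This also stands. It is the unadjusted, one-tailed T2 value after 20% loss. The section on nonadherence and missing data keeps T1 completers in the immediate-effect analysis even if they miss T2, so T1 power can reach 66%. Baseline stigma is collected, and a model that uses it would do better. However, the Primary Outcomes section names only T1 and T2 means, the multilevel regression is described as adjusting for demographic and other variables as needed, and no r is stated. Adjustment therefore cannot be credited with 1128 as the text stands.
- **The inputs may be condensed.** The outcome-by-outcome calculations are not printed, and 0.133 rounds to 0.1; at that d, 1200 per arm gives 83%. This is possible but not shown. It would move the error from n to the reported effect size, and the printed set would still be inconsistent.
- **Harm from country-level results is conjecture.** It is tempting to say that a null result in one country would be read as no effect. No passage says so. The stated aim there is to look for differential effectiveness, and moderation by country is listed among the exploratory subgroup analyses.

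**Conclusion.** The sample size is wrong as written. The printed inputs give about 2008 per arm (2510 after attrition), not 1128 (1410), and no usual choice of alpha or sidedness recovers the stated figure.

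For d = 0.1 the enrolment of 13,500 is ample for the pooled comparison. It does not give 80% power to an unadjusted pairwise comparison within a country: 55% to 66% one-tailed, 45% to 56% two-tailed, depending on time point and retention. These figures take the protocol's d and alpha as given and assume no gain from the baseline score. The upper end assumes no exclusions at T1, although the protocol plans to exclude participants who fail attention checks. With a baseline-adjusted model the one-tailed shortfall would close at r of about 0.50 (T1, no loss) to 0.63 (T2, 20% attrition).

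The error does not by itself require that the pooled comparison be declared confirmatory. That is a design choice for the investigators.

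**What to change.** - Replace 1128 and 1410 with the values that the formula gives: 2008 and 2510 one-tailed, or 2336 and 2920 two-tailed. Alternatively, state the input that yields 1128, for example d of about 0.133, or a baseline correlation of about 0.66 together with the matching baseline-adjusted model as the analysis.
- State that power above 80% for d = 0.1 refers to the comparison pooled over countries (about 97% one-tailed, 95% two-tailed with 3600 per arm).
- Report the country-level power for T1 and T2, and the detectable d with 1200 per arm (about 0.13 one-tailed, 0.14 two-tailed).
- Use the same sidedness in the calculation and in the test. The calculation is one-tailed, the analysis section states no sidedness, and an ANOVA F test has no direction.

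The cost is wording only, with no change in enrolment. The downside is that the stated country-level power becomes less favourable.

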#### Recruitment and Strategies to Improve Adherence to Interventions, Promote Participant Retention, and Complete Follow-Up

Reaching adequate participant enrollment for our target sample size relies on our choice of ProA as a recruitment platform. ProA has a sufficiently large database of registered prospective trial participants in the United States, the United Kingdom, and South Africa. To improve survey completion rates in this trial, we offer payment to all participants. Participants will receive half of their payment after Step 1 of the study and the remaining half after completing Step 2 of the study. If participants spend more than 45 minutes on any phase of the trial, they will be timed out of the experiment. This prevents participants from bottlenecking the survey platform with partially completed questionnaires. We also conducted a pilot trial with 600 participants in the United States only to verify participant retention. In this pilot study, 88% (526/598) of participants returned to complete the follow-up surveys, underscoring the feasibility of this trial [32].

#### Sequence Generation, Allocation Concealment, and Implementation

This 3-arm individual, parallel-group randomized controlled online trial will be hosted and implemented by the Qualtrics survey platform. The platform uses a computer-generated allocation sequence to randomly allocate participants 1:1:1 to the 3 trial arms. The investigators will remain unaware of individual trial arm allocations.

#### Blinding

All co-investigators and researchers involved in the data analyses will remain blinded to the trial arm allocation for the entire duration of the study. Statisticians will also be blinded to the study hypotheses, minimizing the risk of bias.

#### Participant Timeline

Participants will be enrolled over a period of 4 weeks via the ProA platform. Step 1 of the trial (baseline data collection, video viewing, and T1 surveys) will occur on a rolling basis, with Phase 2 (follow-up surveys) taking place 2 weeks later across all arms. After both study phases have been completed, all participants will be offered posttrial access to the intervention video. Their voluntary view times will be recorded as a measure of participant engagement with this health education medium (Table 1).

**Table 1 table1:** Schedule of enrollment, interventions, and assessments.

Trial Information			Enrollment			Allocation			Close-out								
Time point			–t_1_			0			Intervention videos (t_1_)		Surveys (t_1_)		2-week interval		Surveys (t_2_)		Posttrial SAS^a^ video access
**Enrollment procedure**																	
	Eligibility screen	✓															
	Informed consent	✓															
	Allocation				✓												
**Intervention and assessments by arm**																	
	Intervention arms							✓		✓		✓		✓		✓	
	Control arm									✓		✓		✓		✓	

^a^SAS: short, animated storytelling.

